## Abstract

**Introduction:**

Classroom-based active breaks (ABs) have been shown to reduce sedentary time and increase physical activity in primary school children; however, evidence regarding their effects on body composition, physical fitness, cognition and other health-related outcomes remains limited in preschool children. This article describes the rationale and prespecified methods of the MOVI-HIIT study, a cluster-randomised controlled trial (RCT) evaluating a classroom-based, HIIT-inspired ABs intervention delivered through a gamified digital platform to improve body composition, physical fitness, and cognition in children aged 4–6 years. In addition, we outline a nested qualitative study designed to explore teachers’ perceptions of barriers and facilitators to programme implementation and monitoring.

**Methods:**

A RCT was conducted in nine schools in the province of Ciudad Real, Spain. Schools were randomly assigned to the MOVI-HIIT intervention group (*n* = 5) or the control group (*n* = 4). A total of 522 children aged 4–6 years were assessed at baseline (September 2022) and post-intervention (June 2023). The programme included two daily 6-minute HIIT-based ABs (20″/10″ work-to-rest ratio) guided by interactive avatars via a gamified digital platform. The primary outcomes were body composition, physical fitness, and executive function. Secondary outcomes included physical activity, sleep quality, blood pressure, and health-related quality of life. In parallel, a qualitative study using semi-structured interviews and focus groups examined teachers’ perceptions of barriers and facilitators related to the implementation and monitoring of the programme.

**Discussion:**

MOVI-HIIT represents the first intervention in early childhood education to integrate HIIT-based ABs with a gamified digital platform. Its structured, high-intensity exercise, combined with a mixed-methods process evaluation, may provide an innovative and potential reproducible model that can strengthen the evidence on classroom-based physical activity and contribute to creating active and healthy educational environments from early childhood onwards.

**Clinical Trial Registration:**

https://clinicaltrials.gov/study/NCT04863040, identifier NCT04863040.

## Introduction

1

Sedentary behaviour together with low levels of physical activity (PA) among children are major public health concerns because they are linked to poorer health and developmental outcomes (1, 2). Evidence indicates that most European preschool-aged children fail to meet current international PA recommendations, and that their PA levels tend to decline progressively with age (3, 4). This is particularly worrying, as early childhood PA is crucial for healthy growth and the development of motor, cognitive, and social skills.

Schools play a fundamental role in shaping children's daily routines and health behaviour, making them an ideal setting for promoting PA (5). However, a systematic review that included studies conducted in several countries reported that children are insufficiently active during school hours, spending most of this time engaged in sedentary activities (6). Given that children spend a considerable portion of the day at school, implementing strategies to increase PA and reduce sedentary time within this environment is essential.

In recent years, active breaks (ABs) have gained attention as an effective classroom strategy to reduce sedentary behaviour and increase children's PA during the school day (7, 8). Defined as short periods of PA integrated into lessons, ABs aim to interrupt sedentary time without detracting from academic learning, and their viability and feasibility of implementation in school settings have been widely demonstrated (8, 9). Although most studies have focused on demonstrating that ABs are an effective strategy to increase children's PA levels, evidence on their impact in other outcomes remain limited (10, 11). The effects of ABs on physical fitness and body composition have been less explored, and current findings are heterogeneous and inconclusive, possibly due to methodological variability across interventions (10, 12–15). Similarly, although regular PA has been shown to enhance attention and cognitive processing through various neural mechanisms, evidence supporting these effects within classroom-based ABs remains scarce (12, 16, 17). Overall, these findings highlight the scarcity of methodologically robust studies examining the benefits of ABs, particularly in early childhood, an age group that has been scarcely addressed in this type of research (17).

In this context, exploring innovative approaches to enhance the effectiveness of ABs is particularly relevant. High-intensity interval training (HIIT) has emerged as a time-efficient and effective method to improve children's health and fitness, alternating short bouts of vigorous activity with brief recovery periods (18). However, although HIIT appears well suited to children's natural activity patterns (19), evidence on the effectiveness of HIIT interventions in children under 6 years of age remains limited. Classroom-integrated HIIT programmes have been scarcely studied in preschoolers, with insufficient evidence regarding their effects on physical fitness, body composition, and cognition. Therefore, developing an ABs programme grounded in HIIT principles could represent a promising approach to optimize its benefits in early childhood and to provide new evidence in this field.

On the other hand, integrating digital technologies into education can enhance students’ engagement and participation (20). When designed with interactive or gamified features, these tools, including screen-based resources, can encourage movement and support more active learning experiences (21). Therefore, exploring digital platforms to deliver HIIT-based ABs in preschool settings is particularly relevant, as to our knowledge no previous studies have implemented a gamified digital approach for this purpose.

The present study describes the rationale and prespecified methods of a cluster-randomized controlled trial (RCT) —the MOVI-HIIT study — aimed at: (i) evaluating the effectiveness of a classroom-based HIIT inspired AB intervention, delivered through a gamified digital platform, on preschool children's body composition, physical fitness, and executive function; and (ii) exploring teachers’ perceptions of barriers and facilitators to its implementation and monitoring through a nested qualitative study. The trial procedures and analyses are reported here to support transparency and reproducibility, in line with the purpose of a study protocol, while intervention outcomes will be reported separately.

## Methods and analysis

2

This paper is reported in accordance with the SPIRIT statement (22) to enhance completeness and transparency of the prespecified trial methods. The intervention is described using the TIDieR checklist to enable replication (23). Reporting of the nested qualitative component will follow the COREQ checklist (24).

### Design

2.1

This study protocol describes the MOVI-HIIT study, conducted as a two-arm RCT (ClinicalTrials.gov: NCT04863040), including an intervention group (IG) and a control group (CG). Ten schools from different municipalities in the province of Ciudad Real (Castilla-La Mancha region, Spain) were invited to participate. One school declined to participate, noting concerns about potential additional workload for teachers and limited digital skills; therefore, nine schools were included. After agreeing to take part, each school was randomly allocated to either the IG or CG using the StatsDirect statistical software (version 16). Five schools (two public rural, two public urban, and one private urban) were assigned to the IG, where the MOVI-HIIT programme was implemented, while four schools (two public rural and two public urban) were assigned to the CG, which continued usual school activities.

 Figure 1 illustrates the flowchart of the participant recruitment process. The effectiveness of the classroom-integrated MOVI-HIIT intervention was assessed in both groups at baseline and post-intervention.

**Figure 1 F1:**
[figure not shown]
Flow diagram of participant recruitment and allocation (MOVI-HIIT trial) CG, control group; IG, intervention group.

In addition, a nested qualitative study was conducted to explore teachers’ perceptions of the barriers and facilitators related to the implementation and monitoring of the intervention programme.

### Participants and inclusion criteria

2.2

To participate in the study, schools had to be located in the province of Ciudad Real, have at least one classroom in each of the second and third years of preschool education (aged 4 to 6 years), and obtain approval from the School Board for the intervention and the baseline and post-intervention assessments.

Participating schoolchildren were required to be enrolled in the second or third year of preschool education, have no congenital or acquired conditions affecting language acquisition (oral or sign language), and not present any physical or mental disorder identified by parents or teachers that could hinder participation in physical activities. Additionally, children with chronic diseases such as cardiovascular disorders, diabetes, or asthma were excluded if participation was contraindicated, as determined by their pediatrician after reviewing the activity programme.

Since this was a classroom-based intervention, teachers integrated the ABs into the regular school schedule, meaning the programme was delivered to all children in the IG schools. However, only children whose parents or legal guardians provided written informed consent were included as study participants.

### Intervention

2.3

#### MOVI-HIIT! programme: description

2.3.1

The design of the MOVI-HIIT intervention was grounded in the socio-ecological model of behaviour change, addressing factors at the individual, family, and school levels (25). The programme was implemented over one academic year (October 2022 to May 2023) and consisted of two daily 6-minute classroom-based ABs involving physical exercise based on HIIT principles, following a 20"/10" work-to-rest ratio. ABs were delivered through a virtual platform (http://www.movihiit.es) guided by animated avatars, and required no specific equipment, as all classrooms were equipped with interactive screen and internet access.

Each AB followed a structured format: approximately 1 min of animation and exercise explanation, 4 min of physical exercise based on HIIT, and 1 min of breathing and relaxation exercises to facilitate the transition back to academic tasks. The HIIT phase consisted of four exercises (e.g., squats, jumping jacks, or running in place), performed at high intensity (80%–90% of maximum heart rate) for 20 s, interspersed with 10-second recovery periods (65%–75% of maximum heart rate). The sequence of four exercises was repeated twice Figure 2.

**Figure 2 F2:**
[figure not shown]
Session design MOVI-HIIT protocol (2 blocks alternating four exercises of 20 s of high-intensity activity at 85%–90% of maximum heart rate with 10 s of recovery at 65%–75%).

To ensure feasibility and fidelity of implementation, a teacher-oriented virtual platform was designed to guide all ABs. Students were simply required to follow the avatars’ instructions and replicate their movements. The platform is gamified, featuring a ranking system, a weekly progress bar, and a system of daily, weekly, and monthly rewards designed to enhance children's motivation. Figure 3 shows the visual structure and interface of the platform.

**Figure 3 F3:**
[figure not shown]
Visual structure platform.

The preschoolers in the CG received one 45-minute session per week of psychomotor or physical education and continued with their regular classroom activities. Teachers were asked not to implement any changes in their teaching practices during the study period. As an incentive, the research team committed to providing access and training to the MOVI-HIIT platform to CG teachers after the intervention.

#### MOVI-HIIT! organization and delivery

2.3.2

The intervention programme was designed by graduates in Sport and Exercise Sciences, together with Physical Education teachers, and was implemented by the classroom tutors at each participating school. At the beginning of the intervention, teachers attended a 4-hour training workshop in which the research team presented the materials and the virtual platform and provided detailed guidance on their use. In addition, teachers were given a one-week familiarisation period with the programme under the supervision of the research team. To respect teachers’ autonomy and facilitate the integration of the intervention into classroom routines, teachers were allowed to choose the most suitable time of day to implement the HIIT breaks. However, team members recommended carrying them out when schoolchildren (i) had been sitting for a long time, (ii) were not paying attention, or (iii) seemed tired from academic tasks.

#### Implementation and process evaluation

2.3.3

Implementation was evaluated using a mixed-methods process evaluation, including platform-derived delivery metrics, objective checks of exercise intensity and acceptability, and a nested qualitative study exploring teachers’ perceived barriers and facilitators.

##### Intervention fidelity and adherence

2.3.3.1

Prior to implementation, a pilot with heart-rate monitors (Polar A300 watch and H7 chest strap) was conducted to confirm that the HIIT breaks elicited the desired exercise intensity. In week 12, intensity was reassessed *in situ* by fitting heart rate monitors to a random sample of children (*n* = 92) from three intervention schools during the ABs. Programme acceptability was assessed on the same day using a one-item enjoyment scale adapted from the Smileyometer (“How much fun did you have today during the active breaks?”; response options: not at all, somewhat, very much; scored 1–3) (26).

Thus, the process evaluation included indicators of fidelity (exercise intensity), acceptability (children’s enjoyment), delivered dose, and feasibility/ barriers to implementation.

Intervention dose (delivered dose) was tracked by the platform, which automatically logged the number of ABs sessions per class on a weekly and monthly basis and displayed these counts to teachers and students as real-time feedback. When monthly counts were low, the research team conducted follow-up visits with the corresponding teachers to identify implementation barriers and provide specific recommendations.

 When implementation or technical problems were detected, the research team also provided troubleshooting support through the communication channel already established with teachers and, when needed, additional follow-up visits.

Ongoing engagement was supported through a dedicated communication channel (phone number and e-mail) available to teachers throughout the school year, monthly check-ins, and two in-person meetings with classroom teachers (at baseline and after four months). To acknowledge participation and foster motivation, children received small programme-branded incentives (e.g., stickers, drawstring bags, or sports equipment).

After two months of implementation, teachers completed a questionnaire regarding the frequency of HIIT breaks per week, students’ attitudes and behaviour during sessions, perceived barriers to implementation, and suggestions for programme improvement. This information was used to document feasibility and to guide corrective actions during programme delivery.

##### Barriers and facilitators to implementation

2.3.3.2

To understand teachers’ perceptions of the barriers and facilitators to the implementation and monitoring of the intervention, a qualitative study was conducted based on Bronfenbrenner’s socio-ecological model, which conceptualises human behaviour as multifactorial and dynamic (27).

For data collection, semi-structured interviews and focus groups were used, depending on the type of participant. In the case of classroom teachers from participating schools, both methods were applied to explore their knowledge, beliefs, and perceptions regarding the barriers and facilitators to the implementation of the MOVI-HIIT intervention in the classroom.

To gain a deeper understanding of the phenomenon, a purposive convenience sampling strategy with maximum variation was used. Participants were selected from teachers who had implemented the intervention and met the prespecified inclusion criteria. To ensure maximum variation in perspectives, the sample included teachers with different sociodemographic characteristics (sex and age), educational levels (Bachelor's Master's, or Doctorate), professional experience (<10 years, 10–20 years, and >20 years), and school characteristics (public or state-funded; urban or rural), as well as different professional roles (classroom teacher, coordinator, or member of the school leadership team).

The interviews and focus groups were conducted by two researchers trained in qualitative methods. Each session lasted 30–60 min, was video recorded with prior consent, and was conducted via Microsoft Teams.

Transcripts were analysed using thematic analysis. Two researchers independently coded the data and developed themes through an interactive process, resolving discrepancies by discussion (and consultation with a third researcher when needed). Data were managed using ATLAS.ti. Trustworthiness was enhanced through triangulation across data sources (interviews and focus groups) and participant characteristics, and data collection continued until thematic saturation was reached, that is, the point at which additional interviews or focus groups no longer yielded new information or analytical themes relevant to teacher's perceptions across the main participant profiles represented in the sample.

### Outcome measures

2.4

Baseline and post-intervention outcomes (Table 1) were assessed in both groups at two time points: at the beginning (September 2022) and at the end (June 2023) of the school year. All measurements were performed at the schools by trained investigators who were blinded to group allocation to reduce measurement bias and minimise inter-observer variability.

**Table 1 T1:** Study variables.

Type of variable	Specific variables	Tools
Primary variables	Anthropometry: *weight, height, BMI*	Seca 861 and Seca 222
	Body composition: *waist circumference, body fat, fat-free mass*	Flexible measuring tape, Tanita® BC-418 MA 8-electrode
	Physical fitness: *cardiorespiratory fitness, muscular strength, speed-agility, and balance*	PREFIT battery
	Cognition: *inhibition, cognitive flexibility, working memory, general cognitive ability*	NIH Toolbox, Word Span Test, and BADyG-I
Secondary variables	PA, sedentary and sleep quality: *weekly PA, school-day PA, sedentary time, sleep period time, total sleep time, wake after sleep onset, number of awakenings, and sleep efficiency*	Axivity AX3 accelerometer and GENEActiv accelerometer
	Active commuting to/from school	Self-administered questionnaire
	Blood pressure	Omron® M5-I automatic monitor
	Health-related quality of life	Kiddy-KINDL questionnaire
Possible confounding variables	Age	Self-administered questionnaire
	Sex	
	Birth weight	
	Gestational age	
	Parental height and weight	
	Area of residence	
	Country of origin	
	Family socioeconomic status	Parental education and occupation questionnaire
	Food Consumption	Children’s Eating Habits Questionnaire
	Breastfeeding	IFPS questionnaires

BMI, body mass index; PA, physical activity.

#### Primary outcome measures

2.4.1

##### Anthropometric variables

2.4.1.1

Anthropometric measurements were taken twice, and the average value was used for the analysis. Weight was assessed with a calibrated scale (Seca 861) while the child was barefoot and wearing light clothing. Height was measured with a wall-mounted stadiometer (Seca 222), with the child barefoot, standing upright, and the midsagittal plane aligned against the stadiometer's backboard. Children were required to look straight ahead, with their line of vision parallel to the floor. Body mass index (BMI) was calculated from the mean weight and height values, using the standard formula: weight (kg)/height (m^2^).

##### Body composition

2.4.1.2

Waist circumference was measured as the mean of three readings taken at the midpoint between the last rib and the iliac crest, at the end of a normal expiration, using a flexible measuring tape. Body fat percentage and fat-free mass were assessed using a Tanita® BC-418 MA 8-electrode bioelectrical impedance analyser.

##### Physical fitness

2.4.1.3

Health-related physical fitness was assessed using the PREFIT battery (28) which included the following tests:

Cardiorespiratory fitness was assessed using the 20-m shuttle run test (Course Navette), validated to estimate maximal aerobic capacity in preschool children. Participants ran back and forth between two 20-m lines in time with audio signals, starting at 6.5 km·h⁻^1^ and increasing by 0.5 km·h⁻^1^ per minute until exhaustion. Maximal oxygen uptake (VO₂max) was estimated using the PREFIT formula (29).

Muscular strength was assessed using handgrip dynamometry (Takey®, TKK 5401 Grip-D) and the standing long jump test, evaluating upper- and lower-body explosive strength, respectively. In the handgrip test, participants squeezed the dynamometer continuously for 2 s with the right and left hands alternately, performing two trials per hand with short rest intervals; the maximum value (kg) was recorded. In the standing long jump, children jumped horizontally from a standing position, and the best of three attempts was recorded in centimetres (28).

Speed/agility was assessed using the 4 × 10 m shuttle run test, which measures movement speed, agility, and coordination. Children were instructed to run as fast as possible between two lines 10 m apart, completing four shuttles. Two trials were performed, with a 5-minute rest interval between attempts (28).

Balance was assessed using a 30-second one-leg stance test. Children stood on one leg for as long as possible, up to 30 s. Two trials were performed with each leg, and the best result was recorded (28).

##### Cognition

2.4.1.4

Inhibition and cognitive flexibility were assessed using the NIH Toolbox Executive Function Battery, which includes the Flanker Inhibitory Control and Attention Test and the Dimensional Change Card Sort Test (DCCS) (30). In the Flanker task, children identified the left–right orientation of a central stimulus while ignoring flanking stimuli, which could be congruent or incongruent. In the DCCS, stimuli varying by color or shape were presented, and children were required to shift their responses according to the relevant sorting dimension. Both tasks included four practice trials, and a composite score was calculated for each (31).

Working memory was measured using the Word Span Test, which included forward and backward tasks (32). In the forward task, children repeated sequences of two to seven words in the same order, whereas in the backward task, they recalled them in reverse order. The test ended when the child failed both trials at the same sequences length, and a mean score was calculated.

General cognitive ability was assessed using two subtests from the Differential and General Aptitude Battery for Early Childhood Education (BADyG-I) (33): the Quantitative Concepts subtest, which evaluates basic numerical and arithmetic reasoning, and the Vocabulary subtest, which assesses verbal comprehension and general knowledge through image–word association tasks.

#### Secondary outcomes measures

2.4.2

##### Physical activity and sleep quality

2.4.2.1

Twenty-four-hour assessment. A randomly selected subsample of 250 children from both study groups wore an Axivity AX3 accelerometer (Axivity Ltd., UK) on the non-dominant wrist for six consecutive days, including weekends (February–May 2023). Devices were initialized at 100 Hz with a ± 8 g range to record raw triaxial acceleration in gravitational units (g) and data were processed in R using the GGIR package (version 3.0-0) (34). A valid day was defined as at least 10 h of awake wear, and participants provided a minimum of four valid days, including one weekend day. Sleep variables, including sleep period time, total sleep time, wake after sleep onset, number of awakenings, and sleep efficiency, were derived using GGIR algorithms based on sustained inactivity bouts, supported by sleep diaries or, when unavailable, the HDCZA algorithm (35). During waking hours, PA intensities (sedentary, light, moderate, vigorous) were determined using the cut-points proposed by Hildebrand et al. (36, 37).

School-day assessment. To assess PA during school hours, an independent subsample of 150 children from both study groups wore a GENEActiv Original accelerometer (ActivInsights, UK) on the non-dominant wrist from 09:00 to 14:00 during two measurement waves (September–November 2022 and April–May 2023). Devices were initialized at 30 Hz with a ± 8 g dynamic range and recorded raw triaxial acceleration in g. Raw accelerometer data were processed in R (version 4.3.2) using the GGIR package (version 3.0.0) (38), including and initial autocalibration step based on local gravity and temperature according to the algorithm described by van Hees et al. (38). Non-wear time was identified using the standard deviation and range of raw acceleration signals over 60-minute windows with 15-minute increments, following the default GGIR approach (39). Due to the short monitoring duration, physical activity was derived as ActiGraph-equivalent activity counts from raw acceleration using the actilifecounts package (version 1.1.1) (40), according to the method proposed by Neishabouri et al. (41), with a 5-second epoch length. Activity intensity was categorized as sedentary (<306 counts/5 s), light (306–817 counts/5 s), moderate (818–1968 counts/5 s), and vigorous (≥1969 counts/5 s) using the vector magnitude cut-points validated by Chandler et al. for wrist-worn accelerometers in children (42). The school day was analyzed between 09:30 and 13:30 to exclude arrival and departure times, and a valid school day was defined as at least 3 h of wear time within this period after exclusion of non-wear.

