#### Statistical analysis

2.5.2

The statistical analysis will have three phases. The first will consist of verifying that randomisation was effective in creating two comparable groups of schoolchildren, exploring the presence of extreme values and outliers, and assessing the degree of fit of the main variables to the normal distribution.

In the second phase, mixed regression models will be used, taking each outcome variable as the dependent variable, the intervention as a fixed effect (1 = IG and 0 = CG), adjusting for baseline values, age, sex, and including school (cluster) as a random effect. Given that this is a cluster-randomized trial, randomization is the main strategy to minimize selection bias, whereas covariate adjustment is intended primarily to improve precision and account for chance baseline imbalances. The results will be expressed as absolute differences in the changes in the variables between baseline and final measurements [95% confidence interval (95%CI)]. For binary outcomes (e.g., overweight/obesity), logistic regression models will be used, and odds ratios with their 95% CIs will be reported.

In the third phase, a sensitivity analysis will be performed to verify whether the results, using a different variable adjustment method, have the same direction and similar magnitude. To do this, the IG and CG will be compared using the propensity score statistical method to account for the imbalance of covariates in baseline measurements between clusters. The propensity score estimates the effect of the intervention using a causal inference model, explaining what would have happened if all subjects in the IG and CG had the same characteristics at the start of the study. Each subject is matched to a subject with similar characteristics using a caliper of 0.40 using the psmatch2 command.

All analyses will be conducted on an intention-to-treat basis, maintaining participants in their originally assigned IG or CG, regardless of the number of active-HIIT breaks they received, and considering the CONSORT recommendations for this specific type of cluster design (54). In addition to analyses for the total sample, subgroup analyses by age, sex, and socioeconomic status will be conducted.

However, to assess adherence to the intervention, data will be collected on the number of active HIIT breaks each group received. Children in classes that delivered ≥80% of the scheduled breaks will be considered to have received the intervention.

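### The first school-hours accelerometer wave overlaps the start of the active breaks, so adjusting for it as a baseline may pull the school-day activity effect towards zero

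*Protocol article*

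**What the plan says.** All references are to the Protocol article.

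- **Programme dates** (2.3.1, programme description): "The programme was implemented over one academic year (October 2022 to May 2023"), with two six-minute breaks each day.
- **General assessment dates** (2.4, Outcome measures): outcomes were assessed in both groups "at the beginning (September 2022) and at the end (June 2023) of the school year". Table 1 of that section lists "weekly PA, school-day PA, sedentary time, sleep period time" among the secondary variables.
- **School-hours measurement** (2.4.2.1, School-day assessment): "an independent subsample of 150 children from both study groups" wore the device "during two measurement waves (September–November 2022 and April–May 2023"). The analysed window is 09:30 to 13:30.
- **Model** (2.5.2, Statistical analysis): "mixed regression models will be used, taking each outcome variable as the dependent variable", "adjusting for baseline values, age, sex, and including school (cluster) as a random effect". Results are given as "absolute differences in the changes in the variables between baseline and final measurements". No exception is made for school-day activity.

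**The concern.** Three statements do not fit together. General baseline is September 2022, the programme starts in October 2022, and the first school-hours wave runs to the end of November 2022. The second wave (April–May 2023) also differs from the general June 2023 final assessment and falls inside the programme period.

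This matters because school-hours activity should respond as soon as breaks are delivered: the breaks are themselves activity in class. An intervention child measured in wave 1 after the class had started would carry the effect in the value used as baseline. A control child measured on the same day would not. The covariate would then differ between arms because of the treatment, and adjusting for it would remove part of the effect.

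Of the activity measures, this is the one closest to what the breaks do, and the only accelerometer measure taken in two waves. An attenuated result could be read as showing that the breaks add little activity to the school day.

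**Working it through.** The article states no effect size or power for school-day activity, so there is no figure of its own to reproduce. The check uses the dates and the model.

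**1. Calendar overlap.** Taking whole months, wave 1 spans 30 + 31 + 30 = 91 days. October and November account for 61, and 61/91 = 67%. In weekdays it is 43 of 65, or 66%. This is the overlap of the calendar, not the share of children measured late.

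**2. Which value is the baseline?** Section 2.4.2.1 speaks of waves and does not call the first one baseline. There are only two waves, however, and section 2.5.2 applies baseline adjustment to each outcome. Wave 1 is the only earlier value available for school-day activity.

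**3. Effect of adjusting for it.** Let δ be the true effect, f the share of intervention children measured in wave 1 after their class's first break, and b the within-arm slope of the final value on the wave-1 value. Assume that the effect is immediate and as large in wave 1 as in wave 2.

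- Expected arm difference in the final value: δ.
- Expected arm difference in the wave-1 value: f·δ.
- Adjusted estimate: δ − b·(f·δ) = δ(1 − f·b).

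**4. Numbers.** Neither f nor b is in the article. The value f = 2/3 corresponds to intervention children being measured evenly across the wave. The range for b is assumed.

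| f | b = 0.3 | b = 0.5 | b = 0.7 |
|---|---|---|---|
| 0 | 100% | 100% | 100% |
| 1/3 | 90% | 83% | 77% |
| 2/3 | 80% | 67% | 53% |

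For example, f = 2/3 and b = 0.7 gives 1 − 0.467 = 53% of δ retained.

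**5. Simulation check.** The check used 1,000 runs with nine schools (5 versus 4), 17 children per school, an assumed intracluster correlation of 0.03, and least squares without the school random effect. The results agreed with the formula to within about 3 percentage points. At f = 0 the full effect was recovered (1.00 to 1.01).

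**6. Does reporting a difference in change make it worse?** Not in this model. With the baseline value as a covariate in a linear model, using the change or the final value as the dependent variable gives the same intervention coefficient; only the baseline slope moves, from b to b − 1. The loss remains f·b.

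**The case against.** The strongest reply is that the overlap shows a risk, not a bias. The article gives neither the order in which schools were measured nor each school's first break date. Intervention schools may all have been measured before they started, with control schools filling October and November. The stated dates would still hold, f would be 0 and nothing would be lost. The start is given only as a month, and section 2.3.2 adds a training workshop and a one-week familiarisation period at the outset. A journal article commonly leaves a school-by-school calendar to the full protocol. All of this stands. A reader might infer that wave 1 is known to be contaminated, but the article does not support that.

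A second reply is that baseline adjustment cannot apply literally to every outcome, because the 24-hour accelerometry has a single wave (February–May 2023). That is true, but it does not help here: school-day activity does have an earlier wave, and nothing exempts it from the model.

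A reader might also infer from the reporting of differences in change that the loss is the full f, so that only 67% of the effect remains at f = 1/3 and 33% at f = 2/3. Those figures belong to an unadjusted change score, which is not the planned model.

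Finally, it is tempting to drop wave 1 from the main analysis whatever the dates show. With nine schools and 150 children, a valid baseline gives precision and some protection against chance imbalance, which is the purpose that section 2.5.2 gives for covariate adjustment. If the dates are clean, dropping it would discard that for nothing.

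**Conclusion.** The point holds as a conditional risk. The date conflict between sections 2.3.1, 2.4 and 2.4.2.1 is certain. If any intervention child was measured after the class's first break, the planned adjustment biases the school-day activity effect towards zero by the fraction f·b. With b assumed between 0.3 and 0.7, the loss is nil at f = 0, 10% to 23% at f = 1/3 and 20% to 47% at f = 2/3. These sizes rest on assumed f and b and on an immediate, constant effect. They also assume that the breaks fell within the analysed window, since section 3 says that their exact time was not systematically recorded.

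The scope is limited. It is one secondary outcome in a 150-child subsample, no primary outcome depends on it, and the bias runs against the intervention, so it would not create a false claim of benefit. It should be fixed, but it is not a must-fix.

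**What to change.** 1. Compare each child's wave-1 wear dates with the first break logged for that child's class. Section 2.3.3.1 says that the platform logged sessions per class by week and month, so the start can be placed to the week.
2. Reconcile the dates in sections 2.3.1, 2.4 and 2.4.2.1, and state when wave 1 took place in each arm relative to the start of the programme.
3. If every intervention-arm wave-1 measurement precedes the first break, say so and keep the planned baseline adjustment.
4. If not, make the main school-day activity analysis a comparison of the April–May 2023 values, adjusted for age and sex with school as a random effect, without the wave-1 value as covariate and not as a change from it. Keep wave-1 adjustment as a sensitivity analysis only where wave 1 preceded the first break.
5. Choose between steps 3 and 4 on the dates alone, before the arms are compared on this outcome. Section 2.5.2 describes the analysis as still to be done.

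The cost is a date merge and a few lines of analysis text. Under step 4 there is also some loss of precision from giving up the wave-1 covariate.
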